### Outcomes

The primary outcome is the assessment of mean bias (95% CI or precision of bias) for SBP, diastolic BP (DBP), and mean BP (MBP) between invasive and noninvasive BP measurements. The standard deviation of the bias (95% limits of agreement) will be assessed for SBP, DBP, and MBP measurements.

The percentage of signal with artifact, therefore not useable, will be determined. In this regard, secondary outcomes include a reliability index (Qualification Index) for BP epochs and count of qualified epochs.

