### Sample Size

The sample size is chosen based on the recommendations of the ISO 81060 guidelines [17] to determine the feasibility of noninvasive BP monitoring. Based on previous research, study sample size calculations for validation of BP measuring devices showed that 35 individuals is adequate for a high accuracy device (defined as mean BP difference between reference and test device measurement 0, SD 3-6 mmHg) [16]. Consensus was reached that studies performed on the general population should include adult participants; both individuals who are hypertensive and normotensive; ≥30% males and ≥30% females; ≥5% of the reference systolic BP readings ≤100 mmHg, ≥5% with ≥160 mmHg, and ≥20% with ≥140 mmHg; and ≥5% of reference diastolic BP readings ≤60 mmHg, ≥5% with ≥100 mmHg, and ≥20% with ≥85 mmHg. Due to the heterogenicity of patients to be included, we plan to enroll 25 patients in the cardiac catheterization laboratory and 10 patients in the ICU.

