### Statistical Methods

Categorical variables will be reported as counts and percentages; continuous variables will be reported as mean and SD or as median with 25% to 75% IQR according to their distribution as root mean square error. Normality will be assessed by visual inspection of histograms, the computation of Q-Q plots, and the Shapiro-Wilk test. Categorical variables will be compared using chi-square or Fisher exact test as appropriate. Continuous variables will be analyzed using the Student *t* test or the Wilcoxon rank sum test according to their distribution. Categorical variables fall into 3 groups representing the limit of the absolute BP differences: ≤5 mmHg, ≤10 mmHg, and ≤15 mmHg. Both arterial line and Senbiosys device signals will be segmented to epochs of duration (10-45 seconds). BP values will be computed for each epoch. Furthermore, for each epoch, we will compute the reliability index. Epochs with reliability indexes above a given threshold will be qualified for our study. Bland-Altman plots for repeated measures will be used to analyze SBP, DBP, and MBP data collected from the Senbiosys device and the arterial line [18]. Mean difference in scores (bias) and 95% limits of agreement, including the differences between noninvasive and invasive measurements (bias ± 1.96*SD), will be computed. Pearson correlation will be used to characterize the relation between noninvasive and invasive BP measurements. The acceptable bias and precision for arterial pressure measurements were fixed a priori at <5 and 8 mm Hg, respectively [16]. All statistical analyses will be performed using Matlab R2019a (MathWorks).

The null hypothesis is that the difference between invasive and noninvasive methods of BP calculated by Bland-Altman analysis are not within the clinically acceptable range.

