## Discussion

During the last couple of years, a growing number of wearable devices evolved to provide accurate, low-cost, and easily applicable monitoring of vitals parameters using PPG [19], A recent study by Pellaton et al [20] compared SBP and DBP values obtained by radial artery catheterization and those obtained from optical measurements (PPG) at the wrist. Unlike this study, we aim at focusing on the finger as a better location for PPG extraction and consequently BP monitoring. The results of Pellaton et al [20] were quite promising and justifies a further exploration on the finger by the means of SBF2003.

By demonstrating that the Senbiosys SA technology is reliable, we aim to substantially improve BP monitoring. This is particularly relevant both for prevention and ambulatory monitoring. The diagnosis and treatment of hypertension are expected to largely benefit from these advancements.

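### The acceptance limits pool error over all pressures, and nothing stated quantifies how the ring's error changes with BP level, so a ring that compresses readings toward the middle can meet them

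*Protocol article*

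**What the plan says.** Outcomes: "The primary outcome is the assessment of mean bias (95% CI or precision of bias) for SBP, diastolic BP (DBP), and mean BP (MBP"), comparing the invasive and noninvasive methods, with the SD of the bias as a companion measure.

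Statistical Methods: the summary is "Mean difference in scores (bias) and 95% limits of agreement", the latter computed as bias ± 1.96 × SD. The standard is "The acceptable bias and precision for arterial pressure measurements were fixed a priori at <5 and 8 mm Hg, respectively". The null hypothesis is that "the difference between invasive and noninvasive methods of BP calculated by Bland-Altman analysis are not within the clinically acceptable range".

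Three other planned outputs could bear on BP level, all in Statistical Methods:
- "Bland-Altman plots for repeated measures will be used to analyze SBP, DBP, and MBP data".
- "Pearson correlation will be used to characterize the relation between noninvasive and invasive BP measurements".
- Absolute differences are grouped at 5, 10 and 15 mmHg. These groups sort by size of error, not by pressure, and carry no pass mark.

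Sample Size cites a consensus on the range of pressures that a validation study should cover: for SBP, "≥5% of the reference systolic BP readings ≤100 mmHg, ≥5% with ≥160 mmHg, and ≥20% with ≥140 mmHg", with matching DBP cut-offs of 60, 85 and 100 mmHg. No stated analysis uses these cut-offs.

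On purpose, the Discussion says: "The diagnosis and treatment of hypertension are expected to largely benefit from these advancements".

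**The concern.** A pooled bias and a constant pair of limits describe a device well only if its error is about the same at every pressure. The Introduction says that the ring estimates BP from combinations of waveform features, and that accuracy across differing waveform shapes is a main challenge. An estimator of that kind may pull its readings toward an average. Positive errors at low pressures then cancel negative errors at high pressures: the mean bias is near zero, and the level-dependent part of the error is simply absorbed into the SD.

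The high end matters most for the hypertension use that the Discussion hopes for, and there such a ring under-reads. The limits as stated cannot tell it from a ring whose errors of the same total size are random at every pressure.

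**Working it through.** **Inputs from the protocol article.** Limits: bias below 5 and SD 8 mmHg (Statistical Methods), read here as |bias| < 5 and SD ≤ 8 on the observed values. n = 35 (Sample Size). SBP cut-offs 100, 140 and 160; DBP cut-offs 60, 85 and 100 (Sample Size). The protocol gives no figure for level-dependent error, so there is none to reproduce. The sample size of 35 is quoted for a device with mean difference 0 and SD 3-6 mmHg, without alpha or power, and the point does not depend on it.

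**Assumptions.** Reference SBP is normal with mean 130 and SD 20 mmHg. This puts 6.7% at or below 100, 6.7% at or above 160 and 31% at or above 140, so it satisfies the SBP bands. There is one independent value per patient. The difference (ring minus arterial) is -k(x - 130) + e, with k = 0.3 (device slope 0.7) and residual SD s.

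**Step 1: what the pooled figures show.** Mean bias = 0. SD of differences = √((k × reference SD)² + s²).
- s = 5: √(6² + 5²) = 7.81
- s = 4: √(6² + 4²) = 7.21
- s = 3: √(6² + 3²) = 6.71

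All three are below 8.

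**Step 2: what they conceal.** Bias at 100 is 0.3 × 30 = +9 mmHg; at 160 it is -9 mmHg.

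**Step 3: chance of meeting both limits with n = 35 (simulated).** About 61% at s = 5, 83% at s = 4 and 95% at s = 3. Pearson correlation is 0.94 to 0.98, so it gives no warning.

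**Step 4: sensitivity to the reference spread (s = 5, slope 0.7).**

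| Reference SBP SD | SD of differences | Trials meeting both limits |
|---|---|---|
| 18.2 (exactly 5% in each tail) | 7.4 | 77% |
| 20 | 7.8 | 61% |
| 25 | 9.0 | 19% |
| 30 | 10.3 | 3% |

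The 8 mmHg limit therefore caps the compression. The largest k with a true SD of 8 is √(64 - s²) / reference SD. At s = 5 this gives √39/20 = 0.31 for reference SD 20, an error of 9.4 mmHg at 100 and 160. For SD 25 it gives 0.25 and 7.5 mmHg; for SD 30, 0.21 and 6.2 mmHg. The error that can go unnoticed shrinks as the spread widens, but in these cases it stays above the plan's own 5 mmHg bias limit.

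**Step 5: DBP.** A normal curve with exactly 5% at or below 60 and 5% at or above 100 has mean 80 and SD 20/1.645 = 12.16. With k = 0.3 and s = 5, the SD of differences is √(3.65² + 5²) = 6.19. About 99% of trials meet both limits, with bias of +6 at 60 and -6 at 100 (0.3 × 20).

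**Step 6: can 35 patients detect it?** Regressing the difference on the arterial reference (two-sided 5%) has power above 0.99 in each SBP case of Step 3, and about 0.97 in the DBP case of Step 5. Regressing on the mean of the two methods lowers the DBP power to 0.64.

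**Step 7: tail bands.** 5% of 35 is 1.75 patients. If each patient has a 5% chance of falling in a tail band, the chance of one or none there is 0.95^35 + 35 × 0.05 × 0.95^34 = 47%.

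**The case against.** - **Omission.** A slope model or an analysis by band is the kind of detail that a protocol article may leave to an analysis plan, and none is shown. That stands as far as mere absence goes. But the article does fix the limits and the hypothesis, and both are pooled. An added slope analysis would not alter them unless the conclusion were tied to it.
- **The plots look at level.** A reader might infer that the plan ignores BP level altogether. The documents do not support that: a Bland-Altman plot shows difference against level. In the SBP example the correlation of difference with mean is about -0.66 at residual SD 5 and -0.85 at residual SD 3, a visible tilt. What is missing is a number and a consequence.
- **Other outputs would show sizeable errors.** In the example at residual SD 5, only about 48% of differences lie within 5 mmHg, and the limits of agreement are about ±15 mmHg (1.96 × 7.81). This stands, but neither output shows where on the pressure scale, or in which direction, the errors fall.
- **The pass rate depends on an assumed spread.** This stands. Sample Size calls the patients heterogeneous, so a wide spread is plausible, and compression as strong as slope 0.7 would then usually fail. The simulation also uses one value per patient, whereas the plan uses repeated epochs.
- **The stakes rest on a hopeful sentence.** The stated aim is accuracy against the arterial line, and Harms says that the readings are not interpreted clinically in this trial. This limits the point to how the accuracy conclusion may be read.

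**Conclusion.** The point holds in a limited form. For each of SBP, DBP and MBP, acceptability rests on one bias and one SD pooled over pressure. Level-dependent error would be displayed but is neither quantified nor tied to the conclusion.

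Under the stated SBP assumptions, a ring that is wrong by 9 mmHg in opposite directions at 100 and 160 meets both limits in about 61% of trials at residual SD 5 and 95% at residual SD 3. The first figure ranges from 77% down to 3% as the reference SD goes from 18.2 to 30. These results rest on a normal reference distribution, linear compression about the mean and one value per patient.

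Nothing in the documents shows that this ring compresses readings, and a reader should not infer that it does. Nor do the limits let any degree of compression through, because the 8 mmHg SD bounds it. The pooled result remains a valid average; alone, it does not support a claim of accuracy across the pressure range. This is a worthwhile, cheap improvement rather than a fatal flaw.

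**What to change.** In Statistical Methods, for each of SBP, DBP and MBP:

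1. Fit a mixed model of the difference (ring minus arterial) on the arterial reference pressure, with a random patient intercept for the repeated epochs. Report the slope with its 95% CI.
2. For SBP and DBP, report the predicted bias with 95% CI at the Sample Size cut-offs (100, 140 and 160; 60, 85 and 100 mmHg).
3. State that, if the slope is clearly non-zero, regression-based limits of agreement will be reported and the accuracy conclusion will be qualified by BP level, not rested on pooled bias and SD alone.
4. Report bias within the Sample Size bands descriptively only. A 5% tail band may hold about 2 of 35 patients, too few for a useful interval.

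The cost is one extra model per component and one table. The Results section says that data collection is complete, and no new patients are needed. The downsides are imprecise predictions at the extremes and a possibly less favourable conclusion.

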### Analysis

All statistical analyses will be performed using Matlab R2019a. Blinded data analysis will be performed.

### Monitoring

The monitor is an independent trial monitor that will perform all the on-site monitoring activities. The monitor is qualified in the field of the International Standard through training and experience as well as scientific or clinical knowledge. The monitor will ensure that the clinical site understands and follows the protocol; he will review the completeness and accuracy of source data and study documents. Monitoring visits will be performed at the beginning, middle, and end of the study. Source data and documents are accessible to the monitor, and questions are answered during monitoring visits.

### Harms

Since the Senbiosys measurements will not be interpreted in the clinical context, there is no risk of misdiagnoses. Adverse device effect includes the risk of developing a cutaneous allergic reaction. However, this risk is minimal given that the equipment used is of the medical type. In that case, the sensor will be removed earlier, and the patient excluded from the trial. There are no foreseeable interactions with simultaneous medical interventions, as the medical device is on the index finger and does not interfere with other actions. The risk analysis and risk assessment are performed according to EN ISO 1497.

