## Methods

### Study Setting

This is a single-center, single-arm, prospective trial aiming to assess the accuracy of the Senbiosys device to estimate BP versus the invasive BP measurement. The patients will undergo invasive BP estimation and will simultaneously wear the device. This study will enroll 25 adult patients addressed for a coronarography and 10 patients in the intensive care unit (ICU). The intervention period that the devices are worn is between 10 and 15 minutes for each patient. There is no follow-up period after intervention.

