### Participant Timeline

The timeline for enrollment, intervention, and data collection is outlined in Table 1.

**Table 1 table1:** Timetable of patient enrollment and intervention and data collection.

Study schedule	Patient information and inclusion	Intervention period
Visit 1	0	1
Time	≥12h before procedure	0
Patient information	✓^a^	—^b^
Informed consent	✓	—
Baseline characteristics: age, gender, CVRF^c^, etc	✓	—
BP^d^ recordings	—	✓
Primary outcome	—	✓
Secondary outcome	—	✓
Safety outcome	—	✓

^a^This item is included.

^b^This item is not included.

^c^CVRF: cardiovascular risk factor.

^d^BP: blood pressure.

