#### Consent

The study nurse will collect patient information and provide a consent form with details on trial rationale, interventions, and potential benefits and harms. The patients will be given up to 24 hours to consider participation. Patients can withdraw their consent unconditionally, at any time, and without any justification. Medical data that have been collected to date will, however, be analyzed.

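### The Harms section excludes from the trial a patient who has the one named adverse device effect, and this needs reconciling with the safety outcome listed in Table 1

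*Protocol article*

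**What the plan says.** Four places in the protocol article bear on this.

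- **Harms.** "Adverse device effect includes the risk of developing a cutaneous allergic reaction". The risk is called minimal and no rate is given. The consequence of a reaction is then fixed: "In that case, the sensor will be removed earlier, and the patient excluded from the trial".
- **Participant Timeline, Table 1.** A row headed "Safety outcome" is ticked for the intervention period. Neither the table nor the Outcomes section defines it; the latter states that "secondary outcomes include a reliability index (Qualification Index) for BP epochs and count of qualified epochs".
- **Consent.** Patients may withdraw at any time, and for them the text adds: "Medical data that have been collected to date will, however, be analyzed".
- **Study Setting.** Enrolment is 25 coronarography patients and 10 ICU patients. The ring is worn for 10 to 15 minutes, and "There is no follow-up period after intervention".

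**The concern.** The event that should feed the safety outcome is also the event that takes the patient out of the trial. An exclusion after enrolment that is triggered by harm from the device removes patients because of the result being measured. If the rule is followed to the letter, the observed frequency of the named reaction is 0% however many reactions occur.

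The retention rule does not close the gap. It is written for withdrawal of consent, so a patient who leaves for any personal reason keeps their data in the analysis, while for a patient with a reaction the text gives only the exclusion. On the same literal reading, usable blood pressure epochs recorded before the ring came off would also be lost, for a reason connected with the device.

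**Working it through.** **No planned figure is at stake.** The point concerns wording. The only figure to reproduce is enrolment: 25 + 10 = 35, which agrees with the abstract.

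**What can the exclusion clause mean?** The Harms sentence gives two consequences: early removal of the sensor, and exclusion. Participation is one session of 10 to 15 minutes without follow-up, so taking the ring off already ends what the patient does in the study. If the second consequence adds anything, it most naturally concerns the patient's status or data. The weaker meaning, that participation simply ends, remains possible.

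**Size under each meaning, for one reaction among 35 patients** (exact Clopper-Pearson 95% limits):

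- Patient kept for safety: 1/35 = 2.9%. The lower limit is 1 − 0.975^(1/35) = 0.07%. The upper limit solves (1 − p)^35 + 35p(1 − p)^34 = 0.025, which gives p = 14.9%.
- Patient dropped from numerator and denominator: 0/34 = 0%. The lower limit is 0, and the upper limit is 1 − 0.025^(1/34) = 10.3%.
- Patient dropped and replaced by another (the article does not mention replacement): 0/35 = 0%, upper limit 1 − 0.025^(1/35) = 10.0%.

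**How likely is it that the rule is used?** The article gives no reaction rate, so the rates below are assumptions. The chance of at least one reaction in 35 patients is 1 − (1 − p)^35:

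| Assumed rate p | Expected reactions, 35p | Chance of at least one |
|---|---|---|
| 1% | 0.35 | 30% |
| 2% | 0.70 | 51% |
| 5% | 1.75 | 83% |

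**Effect on accuracy.** Only the epochs of the affected patient are at issue. Nothing in the article indicates which way, if any, their loss would move the mean bias.

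**The case against.** The strongest reply is that the Harms sentence describes what happens to the patient and does not define an analysis set. It does not say that the reaction goes unrecorded, that data are deleted, or that the patient leaves the safety count. If the exclusion only means that participation ends, the reaction is counted as 1/35 and nothing is lost. The safety outcome is undefined in this article, and its definition and analysis set may stand in the full protocol. An independent monitor checks the completeness of source data. The risk is described as minimal, the two intervals overlap widely, and no safety threshold is stated that a single case would cross.

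Much of this stands. A reader might infer that the safety outcome cannot count the reaction, or that the adverse device effect rate is zero by construction. The documents do not support that: no passage bars recording or reporting the event. A reader might also take the skin reaction as the only effect foreseen. The wording introduces it as an inclusion, so it is the only one named, and other device effects are untouched by the rule. The missing definition of the safety outcome is not itself a fault in an article.

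What the reply does not remove is the rule as printed. The article states an exclusion tied to a harm from the device, lists a safety outcome, and does not say how the two fit. That is a matter of what the text states, not of detail left to another document.

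**Conclusion.** The point holds as a need to reconcile Harms, Table 1 and Consent. Followed literally, the exclusion rule would drop patients with the named reaction from the safety count: one case would show as 0/34 instead of 1/35. This rests on three conditions: a reaction occurs, the exclusion is applied to the patient's data and not only to further participation, and the full protocol does not already say otherwise.

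The consequence lies mainly in safety reporting. For the primary outcome it is limited to the affected patient's epochs. It is worth correcting because the sentence concerns harm from the device under test and the correction is almost free.

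**What to change.** Leave sensor removal unchanged. Replace the exclusion clause in Harms with wording to this effect: recording stops; the patient stays in the safety numerator and denominator, which comprise all patients on whom the ring was placed; and the reaction is reported. Add that qualified epochs recorded before removal stay in the accuracy analysis, in line with the rule already given for withdrawal of consent.

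The cost is about one sentence. There is one small downside: in the catheterization laboratory two 3-minute aortic recordings are planned, and a patient whose ring comes off early may contribute only the first. The number of such patients should be reported. The Results section says that data collection ended in June 2021, but the change affects only who is counted and reported, so it can still be applied.

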### Ethics and Dissemination

#### Research Ethics Approval

This study is conducted in compliance with the current version of the Declaration of Helsinki. The research project was approved by the local ethics committee of canton Vaud, Switzerland (CER-VD 2020-00996).

#### Protocol Amendments

The principal investigator is responsible for communicating important protocol modifications to the ethics committee and to the competent authorities, including the clinical trial registry (ClinicalTrials.gov NCT04379986).

#### Consent

The study nurse will collect patient information and provide a consent form with details on trial rationale, interventions, and potential benefits and harms. The patients will be given up to 24 hours to consider participation. Patients can withdraw their consent unconditionally, at any time, and without any justification. Medical data that have been collected to date will, however, be analyzed.

#### Confidentiality

The investigators will comply with local privacy laws. Anonymity of the participants will be guaranteed when presenting the data at scientific meetings or publishing them in scientific journals. Participants’ medical information obtained in this study is considered confidential, and disclosure to third parties is prohibited.

